### Sample size calculation

2.2

This study is a multicenter, randomized, double-blind, placebo-controlled trial. The primary outcome is a continuous variable. The allocation ratio between the SXYX group and the placebo group is 1:1. The sample size will be calculated using the formula for comparing two independent means. The formula is as follows:$$n_{1}=n_{2}=2{\left[\frac{(Z_{\alpha /2}+Z_{\beta })\sigma }{\delta }\right]}^{2}$$Based on preliminary data from a small-sample, exploratory pilot study, the peak oxygen consumption (VO_2_ peak) in patients with HFpEF after 6 months of treatment was 20.2 ± 4.8 mL/kg/min in those receiving Chinese herbal medicine, and 18.9 ± 4.2 mL/kg/min in those receiving standard conventional medical therapy. The standard deviations of 4.8 and 4.2 from the preliminary data were used solely to estimate the population standard deviation (*σ*). Based on the OptimEx-Clin Study (21), the latest prognostic studies of percentage of predicted peak VO_2_ in HFpEF (22), and the published results of traditional Chinese medicine for HFpEF with the Qi-deficiency and blood-stasis pattern (23), the minimal clinically important difference for sample size calculation was set at 2.7 mL/kg/min.$$\sigma^{2}=(S_{{}_{1}}^{2}+S_{2}^{2})/2=(4.8^{2}+4.2^{2})/2=20.34$$$$n_{1}=n_{2}=2{\left[\frac{(Z_{\alpha }+Z_{\beta })\sigma }{\delta }\right]}^{2}=2\left[\frac{{\left(1.96+1.282\right)}^{2}\times 20.34}{2.7^{2}}\right]\approx 59$$The calculation yielded approximately 59 patients per group. Accounting for an anticipated 20% dropout rate, the required sample size was adjusted to 74 patients per group, resulting in a total enrollment of 148 patients.

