### Inclusion criteria

2.3

Aged 18–75 years, of any gender.Based on the 2024 *Lancet Seminar “Heart failure with preserved ejection fraction: everything the clinician needs to know”* (3) and the 2019 *European Heart Journal consensus recommendation “How to diagnose heart failure with preserved ejection fraction: the HFA-PEFF diagnostic algorithm: a consensus recommendation from the Heart Failure Association (HFA) of the European Society of Cardiology (ESC)”* (24), the diagnostic criteria for HFpEF were jointly established. The pre-specified diagnostic threshold was set at ≥5 points for the confirmation of HFpEF. All echocardiographic recordings from the different sub-centres were sent to the central research laboratory for unified review. The diagnostic flowchart is shown in Figure 2.Based on the *Guideline for Diagnosis and Treatment of Chronic Heart Failure in Traditional Chinese Medicine (2022)* (25) published in the Journal of Traditional Chinese Medicine in 2022, the diagnostic criteria for the “Qi deficiency and blood stasis pattern” of HFpEF were formulated. The primary symptoms include palpitations, wheezing, fatigue, and shortness of breath. The secondary symptoms are: (i) languidness, disinclination to speak, and easy fatigue with activity; (ii) spontaneous sweating without obvious cause during the day, aggravated after activity; (iii) dull purplish complexion; (iiii) dull purplish lips. For tongue and pulse: the tongue body is purplish (or with ecchymoses, petechiae, or tortuous and cyanotic sublingual collaterals), and the pulse is deep, thready, or feeble and forceless. A diagnosis can be made when two primary symptoms and two secondary symptoms are present, in combination with the tongue and pulse findings. The Traditional Chinese Medicine syndrome score scale is shown in the Table 2.Patients were required to meet the following clinical stability criteria: New York Heart Association (NYHA) functional class II–III; no hospitalisation for acute heart failure, no acute coronary syndrome, and no percutaneous coronary intervention (PCI) or coronary artery bypass grafting (CABG) within the preceding 4 weeks; resting systolic blood pressure maintained within the range of 100–160 mmHg; active myocardial ischaemia rigorously excluded by resting electrocardiography, stress testing, or coronary computed tomography angiography; and a respiratory exchange ratio (RER) of ≥1.10 confirmed on cardiopulmonary exercise testing. In addition, patients’ symptoms and standard conventional medical therapy were required to be stable for at least 2–4 weeks before enrolment.Patients who voluntarily provide written informed consent.

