### Exclusion criteria

2.4

A diagnosis of hypertrophic obstructive cardiomyopathy (HOCM), cardiac amyloidosis, hemochromatosis, Fabry disease, stress (Takotsubo) cardiomyopathy, constrictive pericarditis, muscular dystrophy, severe valvular heart disease, or Unstable coronary artery disease.A diagnosis of stroke or transient ischemic attack (TIA) within the past 3 months, or having undergone coronary artery bypass grafting (CABG), valve replacement surgery, or other major cardiovascular surgery within the past 3 months.Inability to exercise due to lung disease [e.g., forced expiratory volume in 1 s (FEV1) <50% of predicted value, or COPD GOLD stage III–IV], or any condition that may interfere with cardiopulmonary exercise testing.Pregnancy, current breastfeeding, or planning to become pregnant during the study period.Any serious illness that may affect the subject's clinical course, such as: Acute exacerbation of chronic obstructive pulmonary disease (COPD); Acute or chronic liver disease [alanine aminotransferase (ALT) ≥3× the upper limit of normal (ULN)]; Severe renal impairment [defined as serum creatinine (Cr) ≥3 mg/dL, estimated glomerular filtration rate (eGFR) ≤30 mL/min/1.73 m^2^, or receiving regular dialysis]; Anemia [hemoglobin (Hb) <90 g/L]; Gastrointestinal surgery or disease that may affect the absorption of the investigational drug; Acute or chronic pancreatitis; Severe primary hematologic or psychiatric disorders; Any documented active or suspected malignancy, or history of malignancy, within 1 year prior to screening.Any disease (other than heart failure) that, in the investigator's judgment, is associated with a life expectancy of less than 6 months.Known history of allergies, including allergies to multiple drugs or foods, or known allergy to any component of Shengxian Yixin Granule.Inability to exercise, or conditions that, in the investigator's judgment, may affect exercise, inability to perform activities of daily living, or inability to take oral medications.Use of herbal medicines with similar therapeutic effects (e.g., decoctions, patent herbal medicines, or herbal injections) within the past 7 days.Receipt of any investigational therapy other than the study drug.Suspected or documented history of alcohol or drug abuse.Inability to comply with the study assessment schedule for follow-up visits, or judged by the investigator to be unsuitable for continued participation in the trial.

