### Data collection and management

2.15

eCRF completion: Data must be sourced from original documents. All data must be entered in a timely, accurate, complete, standardized, and truthful manner. No items should be left blank. Any corrections must be documented with the reason for change.eCRF review: The clinical research coordinator (CRC) will promptly complete, review, and submit the eCRF, and respond to queries raised by the data manager or clinical research associate (CRA). After data cleaning, the principal investigator will sign to confirm the data.EDC database: A study-specific EDC database will be designed. User acceptance testing (UAT) will be completed before the enrollment of the first patient. All users must complete training before accessing the database.Data entry and verification: Data will be promptly entered and submitted after each visit. The data manager and medical reviewer will review the data and issue queries. After the investigator responds to the queries, the data will be confirmed.Medical coding: Adverse events will be coded using the latest Chinese version of the Medical Dictionary for Regulatory Activities (MedDRA). Concomitant medications will be coded using the second edition of the *Dictionary of Contemporary Drug Trade Names and Aliases*.Blind review and unblinding: After all data tasks are completed, a blind review meeting will be convened to determine the analysis populations and lock the database. After the database is locked, the first unblinding will be performed, during which the statistician will be unblinded only to Group A versus Group B (without knowing which group is SXYX or placebo), followed by statistical analysis. At the final study meeting, the second unblinding will be performed with all participants (investigators, sponsor representatives, and the statistician) together, after which the study report will be signed and finalized.Wearable Device Data Collection and Management1) Device information: Maiya Smart ECG Ring (Maiya Technology, China, model TK30). The device is equipped with a high-performance ECG sensor (GH3228), a PPG sensor (GPSE1602B), and an accelerometer (SC-7A20H), and is compatible with Android 9.0 and iOS 10.0 and above. 2) Pre-trial validation study: To ensure the reliability of data obtained from the wearable device in the target HFpEF population, a pre-trial validation study will be conducted before the main trial is initiated. A total of 32 patients who meet the trial entry criteria (8 from each sub-centre) will be enrolled. Each participant will undergo standard 12-lead electrocardiography (ECG) and pulse oximetry monitoring while wearing the device. Data will be collected under two conditions: (i) at rest (10 min in the supine position), and (ii) immediately after the 6-minute walk test (6MWT). The validation will assess: (i) heart rate accuracy: Bland–Altman analysis will be performed to calculate the mean bias and limits of agreement between the device-derived heart rate and that from the 12-lead ECG; the device will be considered acceptable if the mean absolute error for heart rate is ≤5 beats/min; (ii) oxygen saturation accuracy: the device-recorded SpO_2_ will be compared with that from pulse oximetry, with an acceptable mean absolute error of ≤2%; (iii) step count (distance): device-recorded data will be compared with the actual distance walked during the 6MWT, with an acceptable mean absolute error of ≤5%. 3) Wear time: Participants will wear the ring continuously for 1 week at baseline, week 12, and week 24. To ensure adequate data acquisition, at least 4 valid days are required at each assessment time point. A valid day is defined as a day with wear time ≥23 h (objectively verified by the device's accelerometer and skin-contact sensor) and ≥8 h of valid signal recording. 4) Data quality standards: Within each valid day, at least 8 h of valid ECG/PPG recordings (excluding artefact-contaminated segments) are required. If more than 30% of the recorded signal is classified as artefact (e.g., motion artefact, poor skin contact, or electrical interference), the data from that day will be excluded from analysis. All device-derived data will be reviewed by a blinded central core laboratory, and a random 10% sample will be subjected to additional manual quality checks to ensure inter-rater reliability. 5) Handling of missing data: Multiple imputation (MI) will be employed under the assumption of conditional missing at random (MAR), given the covariates included in the analysis model (baseline values, treatment allocation, visit time) and previous observed values. The imputation model will include all covariates used in the descriptive analysis model for the wearable device data, and will incorporate auxiliary variables that influence the missingness mechanism (e.g., signal quality flags, wear logs) to improve precision. Imputation will be performed only for measures that are complete at baseline but missing at subsequent visits (week 12 or week 24) due to <4 valid days; subjects with complete baseline data missing will not be included in the primary MI analysis, but will be retained in the modified intention-to-treat (mITT) set for other endpoint analyses. Twenty imputed datasets will be generated; the descriptive analysis model will be fitted to each, and the estimates and standard errors will be pooled using Rubin's rules. To explore the potential impact of the MAR assumption on the trend of results within an exploratory framework, a worst-case exploratory scenario analysis will be conducted: missing values in the intervention group will be replaced by the group observed mean +2 standard deviations (in the direction of worsening), and those in the control group by the group observed mean −2 standard deviations (in the direction of improvement). The results of this scenario analysis will be reported descriptively, comparing whether the direction and magnitude of the effect estimates are consistent with those of the primary analysis; all results will be clearly labelled as exploratory, with no formal statistical significance testing or adjustment for multiplicity. 6) Derived outcome measures: Mean heart rate, step count (distance), oxygen saturation, heart rate variability, and nocturnal sleep duration.

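### The wearable's SpO2 acceptance rule has no tracking criterion: if reference saturations vary by an SD of about 2 points or less, a device showing one fixed central value would almost always pass

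*Protocol article*

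**What the plan says.** Section 2.15 (Data collection and management), wearable item 2), describes a validation study to be run before the main trial: "A total of 32 patients who meet the trial entry criteria (8 from each sub-centre) will be enrolled". Each patient is recorded twice, lying at rest and straight after the 6-minute walk.

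Three measures are checked:
- **Heart rate:** "Bland–Altman analysis will be performed to calculate the mean bias and limits of agreement between the device-derived heart rate and that from the 12-lead ECG". Acceptance is a mean absolute error of at most 5 beats/min.
- **Oxygen saturation:** "the device-recorded SpO_2_ will be compared with that from pulse oximetry, with an acceptable mean absolute error of ≤2"%. No other analysis or criterion is named.
- **Step count (distance):** a mean absolute error of at most 5%.

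The article does not say whether the 2% is in percentage points or relative. It does not say whether rest and post-walk readings are judged together or apart. It gives no expected mean or SD for SpO2.

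Oxygen saturation is then one of the derived wearable outcomes in item 6): "Mean heart rate, step count (distance), oxygen saturation, heart rate variability, and nocturnal sleep duration".

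**The concern.** Mean absolute error measures closeness to the reference, not whether the device responds to the patient. When the reference values lie close together, any reading near their centre is close to all of them. A limit that is not set against the spread of the reference can then be met by a device carrying no information about the individual.

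A narrow spread is plausible here. Validation patients must meet the trial's entry criteria. Section 2.3 requires clinical stability ("Patients were required to meet the following clinical stability criteria: New York Heart Association (NYHA) functional class II–III"). Section 2.4 excludes lung disease that prevents exercise, giving as examples "forced expiratory volume in 1 s (FEV1) <50% of predicted value, or COPD GOLD stage III–IV". Nothing in the validation plan asks for a range of saturations to be covered.

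The Discussion presents the wearable assessment as the study's major innovation and names SpO2 among its measures. If the ring passed without tracking saturation, a finding of no between-arm difference in out-of-hospital SpO2 could not be interpreted.

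**Working it through.** **Inputs from the article.** 32 patients, two conditions (64 readings if pooled), limit 2%. The article attaches no pass probability or SD to this rule, so there is no stated figure to reproduce. Every SpO2 mean and SD below is an assumption.

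**Step 1: break-even.** Let the reference be normal with SD s, and let the device always show the centre. Its expected mean absolute error is s × √(2/π) = 0.798s.
- Limit in percentage points: s = 2 / 0.798 = 2.51.
- Limit read as relative, at SpO2 of about 95: 0.02 × 95 = 1.9 points, so s = 1.9 / 0.798 = 2.38.

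**Step 2: chance that a constant passes** (20,000 simulated studies, 64 readings pooled).

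| Reference SD | Constant at centre | Constant 1 point off centre |
|---|---|---|
| 1.5 | 1.00 | 1.00 |
| 2.0 | 0.995 | 0.89 |
| 2.25 | 0.89 | 0.58 |
| 2.5 | 0.52 | 0.23 |
| 2.75 | 0.17 | 0.06 |
| 3.0 | 0.04 | 0.01 |

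A left-skewed reference distribution gives 0.995 at SD 2, 0.70 at 2.5 and 0.22 at 3.

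**Step 3: rest and post-walk modelled separately, then pooled** (values rounded and capped at 100, within-patient correlation 0.5).

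| Rest, mean (SD) | Post-walk, mean (SD) | Constant 95 passes | Constant 96 passes |
|---|---|---|---|
| 96 (1.5) | 95 (2) | >99% | >99% |
| 96 (2) | 95 (2.5) | 78% | 81% |
| 96 (1.5) | 94 (2.5) | 90% | 75% |
| 96 (2) | 94 (3) | 29% | 18% |
| 96 (2) | 92 (4) | 0% | 0% |

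The constant must be well placed: in the first row a device fixed at 98 passes in under 1%.

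**Step 4: what judging the conditions separately does.** At rest alone, with mean 96 and SD 2, a constant 96 passes in 98%. After the walk alone, the best constant tried passes in 98% at SD 2, 57% at SD 2.5 and 14–16% at SD 3. Separate judgement helps if patients desaturate, but does not by itself exclude a constant.

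**Step 5: would limits of agreement be enough?** No. With reference SD 1.5, a centred constant has zero bias and limits of ±1.96 × 1.5 = ±2.9. A genuine unbiased sensor with error SD 1.5 gives the same limits.

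**Step 6: a criterion that separates them.** The same genuine sensor has correlation r = s / √(s² + 1.5²) with the reference. With n = 32, the Fisher-z standard error is 1/√29 = 0.186, and the lower 95% limit exceeds zero when z > 1.96 × 0.186.
- s = 1.5: r = 0.71, z = 0.88; chance of meeting it over 99%.
- s = 1.0: r = 0.55, z = 0.63; about 92% by this approximation, about 89–90% in simulation with readings rounded to whole percent.
- s = 0.5: r = 0.32, z = 0.33; about 42%, or about 32% with rounding.

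A constant has no correlation to estimate and its concordance is zero, so it cannot meet the criterion.

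**The case against.** The strongest objection is that the result turns on an SD the article does not give, and reverses within one point. The narrow range is also not guaranteed: milder lung disease is not excluded by the lung-disease criterion, no SpO2 entry criterion is set, and the post-walk recording may widen the spread. This stands. The point holds only conditionally, and at SD 3 or with marked post-walk desaturation a constant device usually fails.

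The comparator is also favourable to the criticism, because the constant must lie within about 1–2 points of the centre. An uninformative device that fluctuates with the same SD as the reference has an expected error of 1.13 SD, which moves its break-even down to about 1.8. The rule does reject biased, very noisy or badly centred devices. This stands too.

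A reader might infer that an uninformative device would usually pass, that the rule can never show the ring works, or that the between-arm SpO2 comparison is bound to be flat. The documents support none of these. The first two need the missing SD, and passing a rule that a constant could also pass does not make this ring a constant.

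Nor is heart rate a clean contrast. Its agreement analysis is reported, but acceptance also rests on mean absolute error alone. That limit resists a constant only if the heart-rate SD exceeds 5 / 0.798 = 6.3 beats/min, a figure the article also does not give.

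Finally, an article may leave validation detail to the full protocol. But the acceptance rule itself is stated here, and as stated it has this gap.

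**Conclusion.** The point holds in conditional form. The stated SpO2 rule contains no tracking criterion and requires no spread of saturations. If the pooled reference SD is about 2 points or less, a fixed reading near the centre passes almost always (0.995 at SD 2.0), so a pass would not by itself show that the ring tracks saturation. Break-even is at an SD of about 2.5. Which side applies cannot be known before the validation data are in, and the present rule would not reveal it.

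The consequence is limited. SpO2 from the ring is neither a listed secondary outcome (section 2.14.2) nor in the fixed testing sequence (section 2.18). Section 2.15 treats the wearable analysis as descriptive and exploratory, and the primary endpoint is unaffected. This is a cheap improvement.

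**What to change.** In section 2.15, wearable item 2)(ii):
- Keep the 2% limit, state it as percentage points, and apply it separately at rest and after the 6-minute walk.
- Report Bland–Altman bias and limits of agreement for SpO2, as for heart rate.
- Add one criterion a constant cannot meet, such as a device-reference correlation or concordance whose lower 95% limit is above zero. A constant output counts as not meeting it.

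Do not use a rule that the device error must be below that of the sample mean. With reference SD 1.5, a genuine sensor with error SD 1.5 has a mean absolute error of 0.798 × 1.5 = 1.2, the same as the constant, and could be rejected when the range is narrow.

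If the tracking criterion is not met, drop oxygen saturation from the derived outcomes in item 6) or report it as not validated, and keep the other ring measures.

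The cost is a sentence or two in the validation plan and a few lines of code on recordings already planned. The downside is that SpO2 may fail validation, including for a genuine but noisy sensor if saturations vary very little.

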### Visit schedule and assessments

2.13

At Visit 1 and Visit 7, the following will be recorded: patient demographics, medical history, concomitant medications, vital signs, physical examination, as well as assessments including cardiopulmonary exercise testing (CPET), N-terminal pro-brain natriuretic peptide (NT-proBNP), echocardiography, 6MWT, NYHA functional class, EQ-5D score, TCM syndrome score, coagulation function, routine blood, urine, and stool tests, urine pregnancy test, liver and kidney function tests, electrocardiogram (ECG), chest CT (only at Visit 1), and others. At Visit 2, randomization numbers will be assigned, the investigational drug or placebo will be randomly dispensed, and concomitant medications will be recorded. At Visit 1 and Visit 5, the following assessments will be performed: CPET, NT-proBNP, echocardiography, coagulation function, urine pregnancy test, and chest CT (only at Visit 1). At Visit 1, Visit 3, and Visit 5, the following assessments will be performed: 6MWT, NYHA functional class, EQ-5D score, TCM syndrome score, routine blood, urine, and stool tests, liver and kidney function tests, electrocardiogram (ECG), and others. At Visit 1, Visit 3, Visit 4, Visit 5, and Visit 6, major symptoms and signs will be recorded. Adverse events (AEs) and serious adverse events (SAEs) will be monitored and recorded throughout the trial. See Table 3 for the visit schedule and assessments.

**Table 3 T3:** Visit schedule and assessments.

Assessment items	Study phase	Screening period	Enrollment period	Treatment period				
	Visit	1	2	3	4	5	6	7
	Week	-1W	0W	4W ± 3D	8W ± 3D	12W ± 3D	18W ± 3D	24W ± 3D
Screening of participants		√						
Signing of informed consent		√						
Medical interview	General information	√						
	Medical history	√						
	Concomitant medications	√	√	√	√	√	√	√
	Vital signs	√		√		√		√
	Physical examination	√		√		√		√
Efficacy measures	Peak VO_2_	√				√		√
	NT-proBNP	√		√		√		√
	Echocardiography	√				√		√
	NYHA class	√		√		√		√
	6MWT	√		√		√		√
	TCM syndrome scale	√		√		√		√
	Major symptoms/signs	√		√	√	√	√	√
	EQ-5D score	√		√		√		√
	Coagulation function	√				√		√
Safety measures	Routine blood test	√		√		√		√
	Routine urinalysis	√		√		√		√
	Routine stool test+occult blood^a^	√		√		√		√
	Liver function test	√		√		√		√
	Kidney function test	√		√		√		√
	Urine pregnancy test	√				√		
	Electrocardiogram (ECG)	√		√		√		√
	Chest CT	√						
Wearable monitoring devices			√	√	√	√	√	√
Multi-omics analysis		√						√

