Inclusion criteria		√						
Exclusion criteria		√						
Screening number		√						
Randomization number assignment			√					
Dispensing of study drug and diary card			√	√	√	√	√	
Return of study drug and packaging				√	√	√	√	√
Return of diary card				√	√	√	√	√
Overall assessment	Adherence assessment			√	√	√	√	√
	Adverse event reporting and follow-up		√	√	√	√	√	√
	Efficacy assessment			√	√	√	√	√

a Perform stool routine and occult blood tests at Visits 1, 3, 5, and 7 when a bowel movement occurs or when the stool color is found to be black.

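### Wearable data: the ±2 SD worst-case signs contradict their stated direction for steps and SpO2, and Table 3 schedules no ring before the visit where study drug is first dispensed

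*Protocol article*

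**What the plan says.** **Wear weeks.** Section 2.15, wearable item 3: "Participants will wear the ring continuously for 1 week at baseline, week 12, and week 24". The same item adds that "at least 4 valid days are required at each assessment time point". Item 5 is consistent with three windows, since it names only weeks 12 and 24 as follow-up points for imputation.

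**Schedule.** In Table 3 (section 2.13) the row "Wearable monitoring devices" is ticked at Visits 2 to 7 (weeks 0, 4, 8, 12, 18 and 24) and is blank at Visit 1 (week -1). The text of section 2.13 says "At Visit 2, randomization numbers will be assigned, the investigational drug or placebo will be randomly dispensed". The row "Dispensing of study drug and diary card" likewise has its first tick at Visit 2. The last drug return is at Visit 7, and no visit follows it.

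**Worst-case scenario.** Section 2.15, item 5: "missing values in the intervention group will be replaced by the group observed mean +2 standard deviations (in the direction of worsening", with missing control values set to that group's mean minus 2 SD and described as improvement. Item 6 lists the measures: "Mean heart rate, step count (distance), oxygen saturation, heart rate variability, and nocturnal sleep duration". No direction is given for any single measure. The scenario is to be reported descriptively, labelled exploratory and not formally tested.

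**The concern.** There are two separate faults in the wearable plan.

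1. **Sign.** A worst-case scenario is useful only if it pushes missing values against the treatment. Here one pair of signs serves measures that point in different directions. The signs suit heart rate if lower is taken as better. For steps, distance and SpO2 they do the opposite of what the accompanying words say. An analyst who programmes the signs would run a best case for SXYX under a worst-case label.

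2. **Window.** The protocol does not say whether a wear week precedes or follows its visit, and the table shows no ring before the dispensing visit. The printed schedule therefore permits a baseline week that is the first week on treatment. Item 5 uses baseline values as a model covariate and leaves patients with missing baseline data out of the primary imputation analysis, so the definition of that week matters. A pre-dose week that was not recorded cannot be recovered later.

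The Discussion presents the wearable assessment as the study's main novelty, so readers will look at these results even though they are not formally tested.

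**Working it through.** **The plan's own figures.** The protocol states no effect size, missing share or sample size for the device measures. Its only sample size is for peak VO2, and it reproduces: 2 × (1.96 + 1.282)² × 20.34 / 2.7² = 58.65, so 59 per group; 59 / 0.80 = 73.75, so 74 per group and 148 in total. Nothing below touches it.

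**Sign, measure by measure**
- Heart rate: if lower is taken as better, +2 SD for SXYX is worsening. Sign and words agree.
- Step count and distance: higher is better, so +2 SD for SXYX is improvement. Sign and words conflict.
- SpO2: higher is better. Same conflict.
- Heart rate variability and sleep duration: the protocol names no direction, so the rule cannot be checked.
- Comparison: section 2.17 treats peak VO2, where higher is better, the other way round, with the minimum for SXYX and the maximum for placebo.

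**Size if the signs are programmed literally.** Let a share m be missing in each arm, with a common SD.
- SXYX mean after imputation: (1 - m) × mean + m × (mean + 2 SD) = mean + 2m SD.
- Control mean after imputation: mean - 2m SD.
- Shift in SXYX minus control: 2m - (-2m) = 4m SD.

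Where higher is better this shift favours SXYX. The direction in words gives -4m SD, so the two readings differ by 8m SD.

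| Assumed m per arm | Literal signs | Direction in words | Gap |
|---|---|---|---|
| 5% | +0.2 SD | -0.2 SD | 0.4 SD |
| 10% | +0.4 SD | -0.4 SD | 0.8 SD |
| 20% | +0.8 SD | -0.8 SD | 1.6 SD |
| 30% | +1.2 SD | -1.2 SD | 2.4 SD |

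Device missingness is not stated. The 20% row borrows the trial's anticipated dropout rate (section 2.2).

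**SpO2 ceiling.** An assumed 95 ± 3 gives 95 + 2 × 3 = 101%, which is impossible. Whichever arm receives +2 SD can hit this, so a cap is needed under either reading; with a cap the SpO2 shift is smaller than 4m SD.

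**Window: two readings of a tick in Table 3**
- *Wear starts at the visit.* The baseline week is treatment week 1 (7 of 168 days). The week-24 window starts after final drug return and runs past the last visit.
- *The visit reads out the preceding week.* The baseline week lies between Visit 1 and Visit 2, before drug. The ring must then be issued at Visit 1, where nothing is ticked.
- *Either way,* ticks at weeks 4, 8 and 18 do not match three wear weeks.

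**Dilution if baseline were treatment week 1.** Let f be the share of the week-24 effect already present on average in week 1. A change score then keeps 1 - f of the effect. All onset curves here are assumptions:
- Linear onset over 24 weeks: f = 0.5 / 24 = 2%.
- Exponential onset with time constant τ weeks: f = [1 - τ(1 - e^(-1/τ))] / (1 - e^(-24/τ)), which is 5% for τ = 12, 12% for τ = 4 and 37% for τ = 1.

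**The case against.** **On the window.** A reader might infer that the baseline week can only begin once treatment has begun. The documents do not support that. Visit 1 is at week -1 and Visit 2 at week 0, which leaves seven days, and the Visit 2 tick may mark read-out of that week. The week-24 window favours this reading, because a week starting at Visit 7 has no later visit at which to collect the ring. This objection stands against the strong claim. What remains is that ring issue at Visit 1 is not scheduled, that the week is not tied to first dose, and that table and text disagree on the number of windows. Device logistics may be left to a manual, but here a printed schedule conflicts with printed text.

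**On the sign.** A reader might infer that the rule is plainly reversed in favour of SXYX. That also goes too far. The words in parentheses give the right worst-case direction for every measure, and the rule is coherent if the plus sign means toward worsening. Section 2.17 shows that the authors apply the right direction to peak VO2. The fault is a contradiction between sign and words, but the analyst should not have to guess which governs.

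**On consequence.** Device measures are in neither the primary nor the secondary outcome list, nor in the fixed testing sequence, and the scenario is descriptive. A diluted baseline would shrink an SXYX effect rather than inflate it. These points stand and limit the weight of the finding. They do not rescue the check itself: its stated purpose is to compare the direction and magnitude of effects with the main device analysis, and with literal signs it cannot do that for steps or SpO2.

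**Conclusion.** The point holds as an internal contradiction and an unfixed window in the exploratory device analyses.

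- **Worst-case rule.** For step count, distance and SpO2 the printed signs contradict the stated direction and the peak VO2 rule in section 2.17. If programmed literally, the scenario moves the difference 4m SD toward SXYX instead of against it: 0.8 SD at m = 20%, and 0.2 to 1.2 SD for m of 5% to 30%. This assumes equal missingness and a common SD in both arms; the values of m are assumptions.
- **Wear weeks.** Table 3 schedules no ring before the visit of first dispensing, does not tie the baseline week to the time before first dose, and adds ticks that the text does not have. The schedule allows an on-treatment baseline but does not prove one. The resulting dilution cannot be sized from the documents: about 2% under linear onset, up to 37% under the fastest onset tried.

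It would be wrong to conclude that the trial's efficacy result is at risk. The primary endpoint, its sample size and the formal tests are unaffected. The device summaries and their sensitivity check could mislead if carried out as printed.

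**What to change.** 1. **Set the worst-case direction per measure (section 2.15, item 5).** Where higher is better (steps, distance, SpO2), use SXYX mean minus 2 SD and placebo mean plus 2 SD. Use the reverse for heart rate. Name a direction for heart rate variability and for sleep duration. Cap SpO2 at 100%.
2. **Define the windows (section 2.15, item 3).** State that the baseline wear week is the 7 days between Visit 1 and first dose, with the ring issued at Visit 1, and that follow-up wear weeks end at Visits 5 and 7.
3. **Make Table 3 agree.** Show ring issue at Visit 1, and either remove the ticks at weeks 4, 8 and 18 or explain what they record.

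The cost is a few edits to text and table, best made before the first patient is dosed. Two small downsides: some rings go to patients who then fail screening, and a full wear week needs the whole seven days between Visits 1 and 2.
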